**Inclusion Criteria:**

1. At least 18 years of age
2. Have HCV genotype 1 infection and evidence of chronic hepatitis, as confirmed by a liver biopsy completed within three years prior to enrollment in the study (standard of therapy). Patients with compensated liver cirrhosis will be eligible. Patients who have previously been treated under standard of care (Peg-IFN, Ribavrin) and were non-responders, partial responders, or relapsers will also be eligible.
3. Platelet count ≥ 60,000/mm3; absolute neutrophil count ≥ 1000/mm3 ; hemoglobin ≥11.0 g/dL for females or ≥12.0 g/dL for males; serum creatinine </= 1.5 mg/dL
4. Adequately controlled DM
5. Normal or adequately controlled TSH on prescription medication
6. All other clinical laboratory values within normal limits, unless judged not clinically significant by the investigator
7. Capable of understanding instructions, adhering to study schedules and requirements, and willing to provided informed consent

**Exclusion Criteria:**

1. Positive HIV or HbsAg serology
2. Severe psychiatric or neuropsychiatric disorders including, but not limited to uncontrolled severe depression, history of suicidal ideations or suicide attempt(s), as determinate by psychological evaluation
3. Chronic hepatic diseases other than hepatitis C
4. Organ or bone marrow transplant
5. Chronic (greater than 30 days) use of immunosuppressive medications including steroids in doses equivalent to 10 mg of prednisone or higher, 30 days prior to and anytime during the course of the study
6. Female patients who are breast-feeding or have a positive pregnancy test at any time during the study
7. Patients who have had a malignancy diagnosed and/or treated within the past 3 years, except for localized squamous or basal cell cancers treated by local excision
8. Current alcoholism or drug addiction

**Product, Dose, Mode of Administration:** Boceprevir (Victrelis) 200 mg capsules, 800 mg TID po vs. Telaprevir (Incivek) 375mg capsules, 750 mg TID po.

**Additional Therapy, Dose, Mode of Administration for both groups:** Peginterferon alfa-2a 180 mcg s.c., weight-based ribavirin 1200 mg/day po divided twice daily (BID) (patient weight >/= 75kg) and 1000 mg/day po divided twice daily (BID) (patient weight < 75kg). Peginterferon alfa-2b will not be permitted as it is a) less efficacious, b) to keep the co-antiviral treatment comparable and standardized.

**Duration of Treatment:**

Group 1 – Boceprevir (according to product labeling):

- HCV treatment naïve patients: boceprevir for 24 to 44 weeks; PR for 28 to 48 weeks depending on RVR achievement at week 4 of protease inhibitor treatment;
- Relapsers and partial responders: boceprevir for 36 weeks; PR for 36 to 48 weeks depending on RVR achievement at week 4 of protease inhibitor treatment;
- Prior non-responders, or patients with compensated cirrhosis: boceprevir for 44 weeks; PR for 48 weeks

Group 2 – Telaprevir (according to product labeling):

- HCV treatment naïve patients/relapsers: telaprevir for 12 weeks, PR for 24 or 48 weeks depending on RVR achievement at week 4 of protease inhibitor treatment;
- Non-responders and patients with compensated cirrhosis: telaprevir for 12 weeks, PR for 48 weeks

**Criteria for Evaluation:**

Safety and effectiveness assessments will be conducted at study entry, Protease inhibitor therapy week 0, 4, 8, 12, 16, 20, 24, 28, 32, 36, 40, 44 and 48 according to product labeling, if applicable. These will include blood tests, history and complete physical exams. SVR will be assessed at 24 weeks after treatment has been completed.

**Statistical Methods:**

Descriptive statistics will be used for rates (SVR, RVR, end of treatment response, adherence). The primary and secondary endpoints will be determined on an intention-to-treat (ITT) basis. SVR response rates will be analyzed using chi-square test. Equivalency of response rates for the secondary analysis (reduction in treatment length) will be defined as SVR rates that are within the 10% boundaries compared to standard of care. No interim analyses will be performed. As the study is carried out within the regular hepatitis clinic in an unblinded fashion with FDA approved drugs, no data and safety monitoring board will be necessary. Resource use will be prospectively recorded in disaggregated form. Formal cost-effectiveness analysis will be carried out at the end of the study.

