**Study Protocol**

**Title:** Comparative effectiveness and tolerability of boceprevir vs. telaprevir and re-assessment of treatment duration in patients with chronic hepatitis C.

**Duration of Study:** Approximately 48 months

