**Background:**

An estimated 170 million people worldwide are infected with hepatitis C and 4 million of them are in the United States. Around 85% of patients who become infected with hepatitis C fail to clear the virus and become chronic carriers. Among these individuals, 5%to 20% are reported to develop cirrhosis over a period of approximately 20 to 25. For almost a decade, the standard of care (SOC) in patients with chronic hepatitis C has consisted of a 24–48 week course of PEG-IFN-α2a or PEG-IFN-α2b in combination with ribavirin. This therapy leads to a sustained virologic response (SVR) in 42–52% for HCV genotype 1, 65–85% for HCV genotypes 4, 5 or 6 and 76–82% of individuals infected with HCV genotypes 2 or 3.

During the past 10 years, intensive efforts have been made to develop different compounds with antiviral activities against HCV genotype 1, which are referred to as direct acting antiviral agents (DAAs). The clinical development program of the two HCV nonstructural (NS) 3/4A protease inhibitors boceprevir and telaprevir has now been completed. Few reviews, including narrative reviews and randomized trials have been published so far. Their overall conclusion is that adding one of the protease inhibitors to the standard treatment increases the number of SVRs up to 75% in patients who relapse and 40 – 52 % in patients who didn’t respond.

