**Methodology:**

Boceprevir and telaprevir (in combination with peg-interferon alpha 2a and ribavirin [PR]) will be randomly assigned in a 1:1 using a variable block randomization sequence. Boceprevir or telaprevir will be administered through regular clinical care without masking (open label) in previously untreated as well as treatment experienced patients with HCV genotype 1, to be conducted in conformance with Good Clinical Practice (GCP).

This trial consists of two parallel groups: group 1- Boceprevir + PR; group 2 – Telaprevir + PR;

**Type of Blinding:** open-label; however, blinded adjudication of key outcomes, such as adverse events leading to treatment discontinuation, and decisions on treatment cessation due to viral failure will be carried out.

**Allocation concealment:** serially numbered, opaque, sealed envelopes; variable block randomization.

**Sample Size (Including Ratio of Subjects Assigned to Treatments)/Power:** This study is projected to enroll a total of 200 subjects (100:100) in group 1 and 2 respectively.

Given a power of 80% and confidence level of 95% with p-value of 0.05, to determine a 20% difference in tolerability between both drugs, a sample size of 182 is required. Accounting for losses to follow-up, an increase of 10% to the sample size is projected.

**Randomization:** Subjects will be randomized in the two treatment arms in a 1:1 ratio. Randomization will be based on a computer-generated random code.

**Stratification:** Eligible patients will be stratified into 4 groups (treatment naive, treatment experienced; with and without compensated cirrhosis).

**Diagnosis and Criteria for Inclusion:** Adult subjects with CHC HCV genotype 1.

The subject must meet ALL criteria listed below for entry:

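### The equivalence criterion for reduced treatment length has no valid comparison behind it: only drug is randomised, and no group is assigned a reduced course

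*Protocol*

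**What the plan says.** The title announces a "re-assessment of treatment duration in patients with chronic hepatitis C". The Primary and Secondary Objectives cover tolerability, effectiveness and resource use, and do not mention duration. It returns only in Statistical Methods, where equivalency for the "secondary analysis (reduction in treatment length) will be defined as SVR rates that are within the 10% boundaries compared to standard of care". The only test that section names for SVR is given by "SVR response rates will be analyzed using chi-square test".

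On design, Methodology states "This trial consists of two parallel groups", boceprevir + PR and telaprevir + PR, randomised 1:1. The 200 patients come from a 20-point difference in tolerability.

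Duration of Treatment gives both groups the labelled course. In several subgroups the PR length varies "depending on RVR achievement at week 4 of protease inhibitor treatment". Prior non-responders and patients with compensated cirrhosis have 48 weeks of PR in either arm.

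Standard of care is not defined in Statistical Methods. Elsewhere it means treatment without a protease inhibitor: Background says that it "has consisted of a 24–48 week course of PEG-IFN-α2a or PEG-IFN-α2b in combination with ribavirin", and Inclusion Criteria use the term in the same sense.

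**The concern.** An equivalence statement about shorter treatment needs three things: a group given a shorter course, a comparable group given the reference course, and a decision rule that limits the chance of a false claim. The protocol fixes a rule and a margin but provides neither group.

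Short and long courses do exist among the enrolled patients, but patients reach them partly through how they respond. A comparison of SVR between them would mix any effect of length with early response, prior response and cirrhosis. If the criterion were followed as written, the report could call a shorter course equivalent because of who received it, or by chance. Scientific Rationale expects the results to affect treatment recommendations, so such a claim could be acted on.

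**Working it through.** **1. Which comparison could the rule refer to?**

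| Meaning of standard of care | Who receives it | Reduced-length group? |
|---|---|---|
| Peginterferon + ribavirin (Background, Inclusion Criteria) | Neither arm | No concurrent comparator |
| Labelled protease-inhibitor course (Duration of Treatment) | Both arms | None |

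Two comparisons of different lengths remain.
- *Short versus long PR within an arm.* Length depends on prior response, cirrhosis and week-4 RVR, so it is not randomised. The protocol does not spell out which RVR result leads to which length, but the dependence on response is explicit.
- *Between arms.* The protease inhibitor runs 12 weeks for telaprevir and 24 to 44 weeks for boceprevir. This contrast is randomised, but length and drug change together.

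Neither isolates duration.

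**2. What the sample size was built for.** The protocol gives no base rate for its 182. Assume 20% versus 40%; the 20% is the discontinuation rate quoted in Scientific Rationale. With two-sided alpha 0.05 and 80% power:
- uncorrected n per arm = [1.96·√(2·0.3·0.7) + 0.8416·√(0.16 + 0.24)]² / 0.20² = (1.270 + 0.532)² / 0.04 ≈ 81.2
- with continuity correction, (81.2/4)·[1 + √(1 + 4/(81.2·0.20))]² ≈ 90.9, so 91 per arm, **182 in total**
- 182 × 1.10 = 200.2, so 200

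The stated figure reproduces, but it concerns tolerability and not SVR equivalence.

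**3. The rule applied to point estimates.** Inputs: 100 per group, 10% taken as absolute points. The exact binomial probability that the observed rates differ by at most 10 points is:

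| True SVR | True difference | Chance of passing |
|---|---|---|
| 60% v 50% | 10 points | 53% |
| 75% v 65% | 10 points | 53% |
| 75% v 60% | 15 points | 25% |
| 70% v 50% | 20 points | 8% |

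With 50 per group, closer to what a split by duration might give, a true 20-point difference (70% v 50%) passes 17% of the time.

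**4. The rule applied to a confidence interval.** Assume equal true SVR p, between 40% and 75% (the span of the genotype 1 and protease-inhibitor figures in Background). An equal split of 200 gives the smallest standard error, SE = √(2p(1−p)/100).
- p = 0.75: SE = 0.0612; 90% half-width 1.645 × 0.0612 = 10.1 points; 95% half-width 12.0 points
- p = 0.50: SE = 0.0707; 90% half-width 11.6 points; 95% half-width 13.9 points

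The half-width exceeds 10 points throughout, so the interval can fit inside the margin only when the observed rates happen to give a smaller standard error. Exact power of the 90%-interval test with identical true rates is effectively zero at 50–60% and about 3% at 75%.

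For 80% power with two one-sided tests at 5%, n per group = 2p(1−p)(1.645 + 1.282)² / 0.10²:
- p = 0.75: 322 per group, 644 in total
- p = 0.50: 429 per group, 858 in total

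If only non-inferiority were meant (one-sided 0.025), power at 100 per group is Φ(0.10/SE − 1.96), which is 29% at p = 0.50 and 37% at p = 0.75.

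**5. All 200 pooled against a fixed rate.** Treat the benchmark as known and equal to the true rate, with SE = √(p(1−p)/200) and power = 2Φ(0.10/SE − 1.645) − 1.
- p = 0.50: SE = 0.0354, power 76%
- p = 0.75: SE = 0.0306, power 90%

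One arm of 100 gives 28% and 49%.

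**The case against.** The strongest reply is that the low-power figures belong to two-group comparisons. The protocol does not say that its rule compares 100 with 100, and if the reference is a historical rate the comparison is one-sample. That stands. A reader might infer that 200 patients cannot support the margin on any reading, and step 5 shows otherwise. But the protocol names no benchmark rate and no pooling, and closeness to a historical peginterferon–ribavirin rate would say nothing about shortening a protease-inhibitor course.

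A reader might also conclude that the reference is certainly a regimen nobody receives. The protocol's other uses of the term point that way, but Background describes past practice and Scientific Rationale says that both drugs are now entering use, so the labelled course is a possible meaning. The firm statement is that the comparator is undefined and that neither meaning yields a valid comparison.

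It would likewise go too far to say that length varies only with patient response, because it also differs by randomised drug. That contrast does not isolate duration.

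The missing interval is partly a matter for a statistical analysis plan, which is not shown. The text does not say that the rates are observed ones, so the pass rates in step 3 are conditional on a point-estimate reading. An analysis plan could add an interval and an alpha. It could not add a randomised duration contrast or a reduced-length group.

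Finally, one might argue that the rule would penalise success: 42–52% plus or minus 10 points spans 32–62%, so an SVR of 75% would fail. This holds only on the historical reading. Background gives up to 75% for relapsers and 40–52% for prior non-responders, so 75% is not the rate to expect in this mixed population. The conclusion does not rest on it.

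**Conclusion.** The criterion is wrong as written. On either meaning of standard of care there is no valid reduced-length comparison, and this follows from the design whatever the sample size.

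The size of the problem depends on how the rule is applied. On point estimates at 100 versus 100, it passes about 53% of the time at a true 10-point difference and about 25% at 15 points. On a 90% interval, any two-group comparison within 200 patients has a half-width of at least 10.1 points and almost no power. These figures assume an absolute 10-point margin and SVR of 40–75%; the power figures also assume equal true rates. A relative 10% would be a narrower margin and would need more patients.

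A reader might infer that the trial as a whole is compromised. The documents do not support that: the primary objective is tolerability, duration is not a listed objective, and randomisation, the primary comparison and its sample size are untouched. This should be fixed, but it does not rank with defects that threaten the primary result.

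**What to change.** In Statistical Methods, delete the equivalence criterion for treatment length. Replace it with a statement such as: *SVR by assigned (response-guided) treatment duration will be described within each arm with 95% confidence intervals. No conclusion about equivalence or the effect of duration will be drawn, because duration is not randomised.*

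The title can stay if the protocol labels the re-assessment of duration as descriptive. There is no need to move the 10-point margin to the boceprevir–telaprevir comparison, which would be a new analysis with almost no power at this sample size.

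The cost is a wording amendment and the loss of a secondary claim. It needs no extra patients and changes no treatment rule.
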